### Data collection

#### Laboratory visit data.

All measurements will be made at University of Central Lancashire’s physiology and nutrition laboratories and will be undertaken in an identical manner on two occasions, i.e., baseline and post-intervention. The laboratories housed by the University of Central Lancashire are fully accredited by the British Association for Sport & Exercise Sciences, illustrating that they have undergone meticulous inspection and evidenced that; all instrumentation is well maintained in terms of reliability, validity and routine servicing, staff have the appropriate professional and vocational qualifications and that the requisite operational procedures for health and safety are met.

#### Blood pressure and resting heart rate.

Blood pressure and resting heart rate measurements will be undertaken in an up-right seated position at the end of the above-described resting energy expenditure test. Both peripheral measures of systolic and diastolic blood pressure and resting heart rate will be measured via a non-invasive, automated blood pressure monitor (OMRON M2, Kyoto, Japan), adhering to the recommendations specified by the European Society of Hypertension [22]. Three readings will be undertaken, each separated by a period of 1 min [23], and the mean of the last 2 readings used for analysis.

#### Anthropometric measurements.

Anthropometric measures of mass (kg) and stature (m) (without footwear) will be used to calculate body mass index (kg/m^2^). Stature will be measured using a stadiometer (Seca, Hamburg, Germany) and mass will be measured using weighing scales (Seca 875, Hamburg, Germany). In addition, body composition will be examined using a phase-sensitive multifrequency bioelectrical impedance analysis device (Seca mBCA 515, Hamburg, Germany) [24], allowing percentage body fat (%) and fat mass (kg) to be quantified. Finally, waist circumference will be measures at the midway point between the inferior margin of the last rib and the iliac crest and hip circumference around the pelvis at the point of maximum protrusion of the buttocks, without compressing the soft tissues [25]; allowing the waist-to-hip ratio to be quantified.

### Haematological testing

Capillary blood samples will be collected by finger-prick using a disposable lancet after cleaning with a 70% ethanol wipe. Capillary triglyceride, total cholesterol and glucose levels (mmol/L) will immediately be obtained using three handheld analyzers (MulticareIn, Multicare Medical, USA). From these outcomes’ LDL cholesterol (mmol/L) will firstly be quantified using the Anandarja et al., [26] formula using total cholesterol and triglycerides as inputs. In addition, HDL cholesterol (mmol/L) will also be calculated by re-arranging the Chen et al., [27] equation to make HDL the product of the formulae. Both of these approaches have been shown to have excellent similarity to their associated lipoprotein values examined using immunoassay techniques r = 0.948–0.970 [27,28]. The ratios between total and HDL cholesterol and between LDL and HDL cholesterol levels will also be determined in accordance with Millán et al., [29]. Finally, the triglycerides and glucose (TyG index) will be calculated as the natural logarithm of the product of plasma glucose and triglycerides divided by two [29].

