## Materials and methods

### Study design and setting

This study adheres to the latest guidelines for reporting parallel-group randomized trials [18]. The University of Central Lancashire in the city of Preston in Lancashire, Northwest England, will serve as the location for the trial. In accordance with our previous trial, this research follows a 20-day parallel design, incorporating randomized allocation with a placebo control [16] (Figs 1-2). After screening for eligibility and enrolment, participants will then be randomized at the individual level, using a computer program (Random Allocation Software) undertaken by an independent researcher to either a peppermint or placebo group. A permuted block randomization process will be adopted to ensure equal allocation to each trial arm based on the required sample size. Participants and the data analyst will be unaware of the study-group assignments throughout data collection. Indices, pertinent to hypertension, as described in detail below, will be assessed at baseline and after 20-days (post-intervention). In agreement with previous trials involving hypertensive individuals, the primary outcome measure will be the between-group difference in systolic blood pressure from baseline to post-intervention [16,19]. Secondary outcome measures will be between-group differences in anthropometric, haematological, diastolic blood pressure/ resting heart rate, psychological wellbeing and sleep efficacy indices. All experimental visits will take place in the morning and be undertaken in a ≥ 10-hour fasted state. Participants will also be required to arrive hydrated and to avoid strenuous exercise, alcohol, and nutritional supplements 24 h and caffeine 12 h prior.

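### HDL is never measured: it is back-solved from total cholesterol and triglycerides, so HDL and both HDL ratios cannot stand as separate lipid findings

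*Protocol article*

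**What the plan says.** All of the relevant text on the blood variables is in the protocol article, section Haematological testing.

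- What is measured: "Capillary triglyceride, total cholesterol and glucose levels (mmol/L) will immediately be obtained using three handheld analyzers". No HDL assay and no direct LDL assay appears anywhere in the article.
- LDL is calculated first, by a "formula using total cholesterol and triglycerides as inputs".
- HDL is calculated next, by rearranging another published "equation to make HDL the product of the formulae".
- Two ratios follow: "The ratios between total and HDL cholesterol and between LDL and HDL cholesterol levels will also be determined".
- The support offered is: "Both of these approaches have been shown to have excellent similarity to their associated lipoprotein values examined using immunoassay techniques r = 0.948–0.970".

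Under Study design and setting, the blood variables are secondary outcomes: "Secondary outcome measures will be between-group differences in anthropometric, haematological, diastolic blood pressure/ resting heart rate, psychological wellbeing and sleep efficacy indices". The Statistical analysis section compares change from baseline between arms for all outcome measures, with significance at P ≤ 0.05.

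**The concern.** A reader of the results will take HDL, TC:HDL and LDL:HDL as information about HDL. But nothing in the capillary sample is specific to HDL. If HDL is obtained by arithmetic from TC and TG, an effect of peppermint on HDL that does not show in TC or TG cannot be seen. An effect on TC or TG alone can reappear under the name of HDL.

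This could well arise. The Introduction reports that the previous trial in healthy people found a larger fall in triglycerides with peppermint than with placebo. If that recurs, the planned derivation will in general convert it into changes in HDL and in both ratios. Each would be tested and could be reported as a further lipid finding. The Hypotheses section predicts improvement in other cardiometabolic parameters, so such results would count towards a stated hypothesis.

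**Working it through.** The article gives no figure to reproduce here. The question is what the derived variables can depend on.

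**Inputs from the article.** Measured: TC, TG, glucose. Calculated: LDL from TC and TG; HDL from a rearranged second equation; TC:HDL and LDL:HDL from those values.

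**Inferred step.** The article does not say what enters the rearranged equation. LDL is calculated before HDL and no LDL is measured, so the calculated LDL is evidently the input.

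**Step 1: argument without coefficients.** LDL = f(TC, TG). HDL = g(TC, TG, LDL) = g(TC, TG, f(TC, TG)), a function of TC and TG only. TC:HDL and LDL:HDL are therefore also functions of TC and TG only. Two people with the same TC and TG receive the same HDL and the same two ratios, whatever their true HDL. If the second equation also used glucose, which nothing in the text suggests, HDL would still be a function of the measured analytes and not a measurement of HDL.

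**Step 2: general linear form.** The equations are not printed, so their form is assumed:

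- First equation: LDL = a·TC − b·TG − c
- Second equation: LDL = p·(TC − HDL) − q·TG

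Solving the second for HDL gives HDL = TC − (LDL + q·TG)/p. Substituting the first:

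HDL = (1 − a/p)·TC + ((b − q)/p)·TG + c/p

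If a = p, TC cancels and derived HDL depends on TG alone.

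**Step 3: range.** Coefficients were assumed over a = 0.8, 0.9, 1.0; b = 0.2, 0.4, 0.5; p = 0.8, 0.9, 1.0; q = 0.1, 0.2, 0.4; c = 0.7. That is 3 × 3 × 3 × 3 = 81 combinations, each applied to 20,000 simulated TC/TG pairs.

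- The set {TC, TG, LDL, HDL} had rank 2 in all 81. Four named variables carry two dimensions of information.
- Regressing derived HDL on TC and TG gave R² = 1.000 wherever HDL varied. In the 3 × 2 = 6 combinations with a = p and b = q, the formula reduces to the constant c/p and R² is undefined.
- Coefficient on TC: from 1 − 1.0/0.8 = −0.25 to 1 − 0.8/1.0 = +0.20.
- Coefficient on TG: from (0.2 − 0.4)/0.8 = −0.25 to (0.5 − 0.1)/0.8 = +0.50.

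So a fall of 1 mmol/L in TG with TC unchanged would appear as an HDL change between −0.50 and +0.25 mmol/L, depending only on the constants.

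**Step 4: two cases from that range**, both with a = p = 0.9 and c = 0.7, so that c/p = 0.78:

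| b | q | Derived HDL | TG = 1.0 | TG = 2.0 |
|---|---|---|---|---|
| 0.4 | 0.2 | 0.78 + 0.22·TG | 1.00 | 1.22 |
| 0.2 | 0.4 | 0.78 − 0.22·TG | 0.56 | 0.33 |

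The same change in TG gives HDL changes of opposite sign. These are illustrations of the algebra, not estimates for the cited equations.

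**Step 5: count.** The section lists eight blood variables: TG, TC, glucose, LDL, HDL, TC:HDL, LDL:HDL and the TyG index. Four of them (LDL, HDL and the two ratios) are built from TC and TG. Three of those four depend on an HDL that was not measured.

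**The case against.** Several points on the other side are fair.

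- **Derived variables are ordinary.** Body mass index, waist-to-hip ratio and the TyG index are also calculated, and the article says openly that LDL and HDL are calculated. This stands as far as it goes. The difference is that those indices are built from measured components and claim nothing more, whereas HDL is the name of a substance that the trial does not measure.
- **The outcomes are secondary.** This stands. Systolic blood pressure, its analysis and the sample size do not depend on any of this.
- **The article cites validation.** The sources are not at hand, so what they validated cannot be checked. But an equation that must be rearranged to give HDL was evidently published with HDL as an input. Agreement in that direction would not by itself validate HDL solved backwards from an LDL that was itself estimated. It would go too far to say that the cited correlation is wrong or can never apply.
- **The ratios are non-linear.** Their P values can differ from those for TC and TG. This is true, but a different P value from the same two measurements is not new evidence about HDL.

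Three stronger readings are tempting and are not supported. A reader might infer that derived HDL must rise with TG, so that a beneficial fall in TG would always show as a harmful fall in HDL; the coefficients are not in the article and the range above includes both signs. A reader might infer that conclusions on HDL would be false; the documents show only that they would be unsupported, since derived HDL could move with or against true HDL. A reader might also treat this as a threat to the trial's main result, which it is not.

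**Conclusion.** The point holds as a correction to secondary outcomes. As specified, HDL, TC:HDL and LDL:HDL contain nothing beyond the measured analytes. Presenting them as separate lipid findings would be unsupported, and the sign and size of any HDL effect would be set by formula constants applied to TC and TG.

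The dependence needs no coefficients. It rests on the article's list of measured analytes and on one strong inference, that the calculated LDL feeds the rearranged equation. The numerical ranges rest on assumed linear forms and coefficients, and show only that the direction is not fixed by the documents. This is not a detail left to a fuller document: the article specifies the derivation and claims validity for it.

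**What to change.** - Remove HDL, TC:HDL and LDL:HDL from the secondary outcomes. Alternatively, keep them only as descriptive quantities, labelled as transforms of TC and TG, with no test and no conclusion.
- Keep TC and TG as the measured lipid outcomes, and report LDL only as a quantity derived from them.
- Withdraw the r = 0.948–0.970 validity statement for the back-solved HDL.

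The cost is the loss of three secondary outcomes that the collected data cannot estimate, plus a change of wording in the outcome list. If the registry record names these variables, it would need the same change; that record is not at hand. A direct HDL assay would make HDL a legitimate outcome, but the article says data collection began in January 2024, so it could not cover participants already seen. Sample size and the primary analysis do not change.

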### Questionnaires

Sleep quality has been shown to be diminished in patients with hypertension and cardiometabolic disease [30], and supplementation of peppermint has been demonstrated to enhance sleep quality [31]. Therefore, general sleep quality will be examined using the Pittsburgh sleep quality index [32], daytime sleepiness using the Epworth Sleepiness Scale [33] and symptoms of insomnolence via the Insomnia Severity Index [34]. These questionnaires will be utilized cooperatively to provide a collective representation of sleep efficacy. The Pittsburgh sleep quality index measure consists of 19 individual items, creating 7 components (subjective sleep quality, sleep latency, sleep duration, sleep efficiency, sleep disturbance, use of sleep medication, and daytime dysfunction) that produce a global score ranging from 0 to 21, with lower scores denoting a healthier sleep quality. The Epworth Sleepiness Scale con-sists of a list of eight scenarios in which tendency to become sleepy is rated on a scale of 0–3. The total score is the sum of these responses and ranges from 0 to 24, with higher scores indicating increased sleepiness. The Insomnia Severity Index features seven questions in which sleep difficulty is rated on a scale of 0–4. The total score is the sum of these responses and ranges from 0 to 28, with higher scores indicating greater sleep difficulty.

Because psychological wellbeing is lower in those with hypertension and cardiometabolic disease [35], general psychological wellbeing will be examine using the COOP WONCA questionnaire [36], depressive symptoms using the Beck Depression Inventory [37] and state/ trait anxiety with the State Trait Anxiety Inventory [38]. Once again, these scales will be utilized conjunctively to provide a collective depiction of psychological wellbeing. These scales were utilized conjunctively to provide a collective depiction of psychological wellbeing. The COOP WONCA questionnaire comprises six scales (physical fitness, feelings, daily activities, social activities, change in health and over-all health) designed to measure functional health status on a scale ranging from 1 to 5. The final score is the mean of the six scales, with a higher score indicating reduced functional health. The Beck Depression Inventory is a 21-item questionnaire in which depressive symptoms are rated on a scale of 0–3. The total score is the sum of these responses and ranges from 0 to 63, with higher scores indicating greater depression. Finally, the State-Trait Anxiety Inventory uses 20 items to assess trait anxiety and 20 to examine state anxiety, rated on a scale of 0–4. The total score for both trait anxiety and state anxiety is the sum of these responses foreach component and scores range from 20 to 80, with higher scores denoting greater anxiety.

### Data management

The collection and storage of data will adhere to the standard requirements of the UK Data Protection Act 2018. Data will be entered onto electronic spreadsheets, which will be stored on a secure university server using Microsoft OneDrive. All data will be treated confidentially and anonymized for evaluation. Hard copies of data and documents will be kept in a locked and secure filing cabinet for the duration of the study. Following completion of the study, data will be transferred to the University of Central Lancashire Research Data Archive (CLOK), where it will be kept for 7 years. Hard copies will be disposed of confidentially and electronic data deleted after this period of time.

### Statistical analysis

Continuous experimental variables will be presented as mean values along with their corresponding standard deviations. To compare compliance levels between the trial arms, between-group linear mixed effects models will be utilized. In these models, group will be treated as a fixed factor, and random intercepts will be included for participants.

All analyses of the intervention-based data will follow an intention-to-treat approach. To determine the effects of the intervention on all of the outcome measures, differences in the changes from baseline to 20-days between the two trial arms will be examined using linear mixed-effects models with a group modelled as a fixed factor and random intercepts by participants adopted, employing the restricted maximum-likelihood method [16]. For linear mixed models, the mean difference between groups in changes from baseline to 20-days (*b*) and 95% confidence intervals of the difference will be presented. As the experimental questionnaires yield data that are predominantly ordinal in nature, the aforementioned effects of the intervention between trial arms will be examined using Mann-Whitney U tests. Effect sizes will be calculated for the changes from baseline to 20-days between the two groups, using Cohen’s d, in accordance with McGough & Faraone, [39]. Cohen’s *d* values will be interpreted as 0.2 = small, 0.5 = medium, and 0.8 = large [40]. The efficacy of blinding will be assessed using a one-way chi-square (*Χ*^2^) goodness-of-fit test [16]. Chi-square analyses will be calculated using Monte-Carlo simulation to determine probability values. All statistical analyses will be performed using SPSS v29 (IBM Inc., SPSS, Chicago, IL, USA), and statistical significance will be considered at a P ≤ 0.05 level.

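### The primary mixed model has one change score per participant, so its random intercept cannot be estimated and the analysis is a two-sample t-test on changes without baseline adjustment

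*Protocol article*

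**What the plan says.** Under Study design and setting, the outcome indices "will be assessed at baseline and after 20-days (post-intervention"), and "the primary outcome measure will be the between-group difference in systolic blood pressure from baseline to post-intervention". Under Blood pressure and resting heart rate, three readings are taken at a visit, with "the mean of the last 2 readings used for analysis".

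Under Statistical analysis, "differences in the changes from baseline to 20-days between the two trial arms will be examined" by "linear mixed-effects models with a group modelled as a fixed factor and random intercepts by participants adopted, employing the restricted maximum-likelihood method". The coefficient to be reported, with a 95% confidence interval, is "the mean difference between groups in changes from baseline to 20-days". Group is the only fixed factor named. Compliance is compared between arms with the same structure: "In these models, group will be treated as a fixed factor, and random intercepts will be included for participants". The section also states: "All analyses of the intervention-based data will follow an intention-to-treat approach". The planned software is SPSS v29.

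**The concern.** A random intercept per participant describes correlation among several observations on the same person. Here the response is a change between two visits, and each visit gives one SBP value, so there is only one observation per person and no within-person correlation to model. The same is true of percentage compliance, which is worked out once from the returned supplement.

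The section states this model rather than leaving it to another document, so it is a specification fault and not an omission. Three things follow:

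- An analyst who runs it as written may meet a convergence warning and have to choose a repair after seeing data.
- Calling it a mixed model suggests that it makes use of participants with incomplete data. A change-score model cannot do that.
- Baseline SBP is measured on everyone but is not used as a covariate, which gives away precision.

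**Working it through.** **Inputs from the protocol article.** Two assessments; one averaged SBP per visit; response = change; fixed effect = group; participant random intercept; REML. Sample size section: d = 0.85, α = 5%, directional hypothesis, 80% power, 36 evaluable, 10% dropout, 40 randomised.

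**The plan's own figure.** One-sided 5%, 80% power: 2 × (1.645 + 0.842)² / 0.85² = 17.1, so 18 per arm and 36 in total. The noncentral t gives power 0.803 at 18 per arm, and 36 / 0.9 = 40. The stated size reproduces and is not in dispute here.

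**Step 1: identifiability.** For participant i, change_i = β₀ + b·group_i + u_i + e_i, with Var(u) = σ²_u and Var(e) = σ²_e. With one row each, the covariance matrix is V = (σ²_u + σ²_e)·I. The likelihood depends on the two variances only through their sum. As a numerical check, 36 changes were simulated (18 per arm, SD 1, true difference −0.85):

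| Share of variance given to the random intercept | REML log-likelihood | b | SE of b |
|---|---|---|---|
| 0% | −18.5326 | −0.938 | 0.320 |
| 25% | −18.5326 | −0.938 | 0.320 |
| 50% | −18.5326 | −0.938 | 0.320 |
| 75% | −18.5326 | −0.938 | 0.320 |
| 99% | −18.5326 | −0.938 | 0.320 |

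The likelihood is flat along the split. The effect and its standard error do not move, and they equal the pooled two-sample t-test on the same data (−0.938 / 0.320 = −2.93, 34 df).

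**Step 2: what software may print.** The same data fitted with Python's statsmodels gave a warning that the Hessian was not positive definite, variances of 0.462 and 0.462, and a printed SE for b of 0.154. The variances themselves imply √[(0.462 + 0.462) × 2/18] = 0.320, the correct value. The printed figure comes from inverting a singular matrix in that package and is not a property of the data. SPSS v29 was not run.

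**Step 3: missing day-20 values.** A participant without a day-20 value has no change and so no row. At 10% dropout, 0.10 × 40 = 4 are not in the model.

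**Step 4: precision forgone.** Assume equal SD σ at both visits and correlation ρ. The variance per participant is 2σ²(1 − ρ) for a change and σ²(1 − ρ²) after baseline adjustment. The ratio of standard errors is √[(1 − ρ²) / (2(1 − ρ))] = √[(1 + ρ)/2].

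| Assumed ρ | SE ratio, adjusted to change | Reduction |
|---|---|---|
| 0.4 | √0.70 = 0.837 | 16% |
| 0.6 | √0.80 = 0.894 | 11% |
| 0.8 | √0.90 = 0.949 | 5% |

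The article gives no correlation, so this is a range and not an estimate for this trial.

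**The case against.** The strongest reply is that the redundancy is harmless. The only unidentified quantity is the split of two nuisance variances. The plan reports the difference in mean change, its interval and Cohen's d, none of which needs the split. Any software that computes the standard error from the total variance returns the t-test. This stands, and it limits the point to a redundant and less efficient model.

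Three stronger readings are tempting, and the documents do not support them.

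- *The treatment effect is not identifiable, or its standard error will be far too small.* Step 1 rules out the first. The second rests on the behaviour of one Python package, while the plan names SPSS.
- *The model halves the effect.* If the raw values of both visits were entered with group as the only fixed term, the coefficient would average a zero difference at baseline with the day-20 difference, which is half the effect. But the section says that changes are examined and defines the coefficient as a difference in changes, so this is not the model described.
- *The intention-to-treat statement is false, or missing data have been overlooked.* Analysing people in their randomised arm is compatible with the text, missing-data rules may sit in an analysis plan that is not shown, and the loss of 4 is allowed for in the sample size. What remains is that this model cannot itself use those participants.

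Bias from the missing rows also depends on the dropout pattern. In a simulation with about 10% missing, ρ = 0.6 and dropout related to baseline in opposite directions by arm, complete-case change scores averaged −0.781 against a true −0.85, and baseline adjustment gave −0.851. With dropout related to baseline in the same direction in both arms, the two methods were nearly equal (−0.835 and −0.837).

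**Conclusion.** The point holds in a limited form. The random intercepts in the primary and compliance models cannot be separated from the residual, which is algebra and needs no assumption beyond one value per participant. The primary analysis is in effect a two-sample t-test on changes. It estimates the quantity the plan defines, so neither the primary result nor the sample size is invalidated.

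The cost has three parts: possible convergence warnings or unreliable printed standard errors, depending on software; a standard error roughly 5% to 16% larger than it would shrink to with baseline adjustment, stated as the reduction available for assumed correlations of 0.8 down to 0.4; and no row for about 4 of 40 participants at the planned dropout. Whether those missing rows cause bias depends on a dropout mechanism that the article does not give.

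**What to change.** Replace the primary model, before unblinding, with one of the following.

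1. **Two rows per participant** (baseline and day 20): fixed time and group-by-time effects, a baseline mean common to both arms, unstructured within-participant covariance, REML. Include every randomised participant with a baseline value. The day-20 contrast between arms is the primary estimate.
2. **More simply**, a linear model of day-20 SBP on group and baseline SBP, one row per participant. This still omits those without a day-20 value, and the text should say so.

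With a single follow-up and complete baselines, the two should give practically the same contrast. A participant with only a baseline informs the baseline distribution and not the regression of day 20 on baseline. The gain over change scores therefore comes mainly from conditioning on baseline, and option 1 should not be presented as recovering the lost day-20 information.

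Apply the same structure to the other outcomes now assigned to this mixed model. Compare compliance with a two-sample test and delete its random intercept. State, here or in the analysis plan, how missing day-20 values are handled under the intention-to-treat heading.

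The cost is wording only: the same data and the same software serve.

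### The seven questionnaire scores get a rank test on change scores but a mean-based effect size with no matching interval, and using the baseline only by subtraction gives up power

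*Protocol article*

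**What the plan says.** Four consecutive statements in the Statistical analysis section of the protocol article bear on the questionnaires.

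- The mixed model is given the widest scope, "To determine the effects of the intervention on all of the outcome measures". Its target is the between-arm contrast in change: "differences in the changes from baseline to 20-days between the two trial arms will be examined using linear mixed-effects models".
- The interval is tied to that model. "For linear mixed models, the mean difference between groups in changes from baseline to 20-days" will be presented with its 95% confidence interval.
- The questionnaires are then taken out and given the Mann-Whitney U test instead. The reason stated is "As the experimental questionnaires yield data that are predominantly ordinal in nature".
- The effect-size sentence makes no exception for them: "Effect sizes will be calculated for the changes from baseline to 20-days between the two groups, using Cohen’s d". Values of 0.2, 0.5 and 0.8 are to be read as small, medium and large.

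The Questionnaires section defines seven scores from six instruments. Three concern sleep: "general sleep quality will be examined using the Pittsburgh sleep quality index [32], daytime sleepiness using the Epworth Sleepiness Scale [33", plus the Insomnia Severity Index. Four concern wellbeing: COOP WONCA, the Beck inventory, and separate state and trait anxiety totals. All seven are secondary outcomes.

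**The concern.** The reason given for leaving the mixed model is that the scores are mainly ordinal. Subtracting a baseline, and dividing a mean difference by a standard deviation, both rely on roughly equal spacing. If the spacing is doubtful, d is a poor companion to the rank test. If the spacing is good enough for d, the stated reason for giving up the mean difference and its interval is weak.

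Two practical consequences follow. First, each sleep and wellbeing result would carry a P value about ranks and a verbal size label about means, with no stated interval for either. With about 18 evaluable participants per arm, precision is what a reader most needs. Second, ranking a subtracted score uses the baseline inefficiently, although it is already collected and could serve as a covariate.

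**Working it through.** **1. What is applied to what.** The Mann-Whitney sentence refers back to effects already described, and the only effects described before it are between-arm differences in change from baseline. The Cohen's d sentence also refers to changes and covers both groups without restriction. So change scores and d for the questionnaires follow from the text, though neither is spelled out for them by name.

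**2. Number of scores.** 3 sleep + 4 wellbeing = 7.

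**3. Sample size behind the check.** The document gives no sample size for the questionnaires, so the primary-outcome figure is used. With d = 0.85, one-sided α = 0.05 and power 0.80, the two-sample calculation gives 18 per arm, 36 in total (noncentral t power 0.803). Then 36 / 0.90 = 40. Both stated totals reproduce, and this point does not depend on them.

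**4. Test and effect size are different quantities.** Mann-Whitney addresses P(A > B) + ½P(tie). Cohen's d is (mean A − mean B) / pooled SD. An invented example with 18 change scores per arm shows that they can part:

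- Arm A: 14 scores of −1 and 4 of +9. Mean = (−14 + 36)/18 = 1.22.
- Arm B: 14 scores of 0 and 4 of +1. Mean = 4/18 = 0.22.
- Only the four +9 values exceed anything in B, and there are no ties, so the probability of superiority is 4/18 = 0.22. Arm A ranks lower, Mann-Whitney P = 0.0025.
- Mean difference = +1.0 and d = +0.33, which points the other way (t-test P = 0.33).

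This shows that it can happen, not how often. In simulations of 5,000 trials under other assumed distributions, Mann-Whitney and the t-test on the same changes disagreed on significance in about 7% (near-normal changes) to 9% (skewed, floor-bounded changes) of trials. The signs of the two effects differed in about 1% to 4%.

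**5. Power lost by using the baseline only through subtraction.** The documents give no distribution for any questionnaire score, so one is assumed: rounded gamma scores (shape 1.2, scale 6), Gaussian-copula correlation 0.6 between baseline and day 20, 18 per arm, two-sided 0.05, 4,000 trials per scenario, and day-20 scores 40% lower in one arm. Independent runs gave:

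| Analysis | Power |
|---|---|
| Mann-Whitney on changes | 29–31% |
| Rank ANCOVA, day-20 score adjusted for baseline | 40–41% |
| Linear ANCOVA, day-20 score adjusted for baseline (one run) | 44% |

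The gain from the rank-adjusted analysis is about 10 percentage points (0.414 − 0.309 = 0.105 in one run). Type I error of Mann-Whitney on changes was 4.5–4.8% with no effect, so the planned test holds its level. The adjusted analyses were also at nominal level.

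**The case against.** The strongest reply is that nothing here is invalid. Mann-Whitney on change scores holds its type I error, and reporting d beside a rank test is common. The text says the data are predominantly ordinal, not that differences have no meaning. Every score is itself a sum or mean of items, so the choice can be read as one of robustness. This stands. The point is a mismatch and a loss of efficiency, not a faulty P value.

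A reader might infer that the labels from d will often contradict the test. The documents do not support that. Under the skewed scenario, the label from d and the label implied by the rank effect differed in about 30% of simulated trials. With perfectly normal data they still differed in 16–18%, because estimates at this sample size straddle the cut-points. Sign disagreement was 12–13% with no effect and 4% with the 40% reduction, but was already 7.5% with normal data and no effect. It never coincided with a significant Mann-Whitney result in 16,000 runs. These figures are illustrative only.

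A reader might also infer that no interval will ever be reported. The article does not say so. It is condensed, and a fuller analysis plan may name one. What it does fix is d as the effect size, with an interval tied only to the mixed models.

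Finally, the power gap comes from baseline adjustment, not from the mismatch between test and effect size. That is correct, and the two are kept apart here.

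**Conclusion.** The point holds as a minor improvement. The Statistical analysis section assigns the questionnaires to two methods in turn and then pairs a valid rank test with an effect size that does not correspond to it. The baseline score enters only by subtraction, at a cost of about 10 percentage points of power in the scenario examined.

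That size rests on an assumed score shape, correlation and effect. It resembles a skewed scale such as the Beck inventory, should not be carried over unchanged to all seven scores, and would change with a different correlation. The reading that d and change scores apply to the questionnaires is the natural one but is not explicit. If something else was intended, the wording still needs to say so. Systolic blood pressure, the sample size and trial conduct are untouched.

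**What to change.** Three changes to the Statistical analysis section, settled before any unblinded analysis:

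1. Limit the mixed-model sentence to the measured continuous outcomes, so that it no longer overlaps with the questionnaire sentence.
2. For each of the seven questionnaire scores, compare the day-20 score between arms with its own baseline score as covariate, using one prespecified method: rank ANCOVA, or proportional-odds regression.
3. In place of Cohen's d for these scores, report an effect measure with a 95% confidence interval that matches the chosen method: the odds ratio for proportional odds, or the probability of superiority, U/(n1 × n2), if a rank test is kept.

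The cost is a few sentences and a little extra analysis, with no new data. There are real downsides. Both measures are less familiar to readers than d. Proportional odds adds an assumption and meets many sparse categories at about 18 per arm (the Beck total alone can take 64 values, 0 to 63). It fitted without failure in a small simulation of 60 trials per scenario, which is limited reassurance.
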